### Recruitment procedure

The participants were recruited between 2 November 2021 and 30 November 2021. Informed consent from head-teachers, parents and assent from children was sought by trained research team for their participation in screening for the research study and for participation into the enrolment of the research study. Since the current study is school based, the permission to conduct the study was obtained from the school education department. Following informed consents and assents forms for the screening phase, the self-rated PSC was administered by the trained AT to screen adolescents for psychosocial distress in a private location in school settings for maintaining confidentiality. Participants meeting the eligibility criteria were enrolled for the study.

### Intervention

#### EASE intervention

Developed by the WHO, EASE is a brief, group psychological intervention programme^11^ based on evidence-informed techniques that are empirically supported for young adolescents living with symptoms of internalising disorders.^17^ The intervention is comprised of 7 weekly group sessions lasting 90 min for the young adolescents and is accompanied by three group sessions for their caregivers, each lasting approximately 90 min. The young adolescent sessions involve the following empirically supported components: psychoeducation, problem-solving, stress management, behavioural activation and relapse prevention. The caregiver sessions involve psychoeducation, active listening, quality time, praise, caregiver self-care and relapse prevention. The adolescent sessions will be delivered on weekly basis, and the three caregiver sessions are delivered at the third, fifth and seventh weeks of the adolescent intervention. Home practice of the EASE strategies is encouraged between each session for both adolescents and caregivers. Each EASE session is delivered by one primary facilitator and a cofacilitator.

#### Training and supervision of non-specialist facilitators in EASE intervention

EASE delivery school counsellors will be graduates with little or no prior experience of delivering targeted psychological interventions. EASE school counsellors will be selected from these fresh graduate students (having a bachelor degree in psychology) based on interviews and successful delivery of practice cases (at least one group each) under close supervision.

EASE school counsellors will receive 8 days (80–90 hours) of training by the master trainers of the intervention. Intervention training includes education on adversity and its impact on mental health, basic counselling skills, training in managing distressed participants, delivering EASE, skills in group facilitation and facilitator self-care. Further, school counsellors will have conducted at least one practice EASE intervention group under close supervision. Only school counsellors assessed as being competent (see quality control below) will be recruited to deliver the EASE intervention in the trial phase.

#### Supervision

Weekly supervision will be provided to EASE school counsellors by an appropriately qualified and trained supervisor for EASE with a good understanding of the young adolescent project to ensure fidelity of guidance provided, and to support school counsellors; in turn, this supervisor will be supported by clinical supervisors who have been involved in the development or training of EASE on a weekly to fortnightly basis and via Skype. Supervision will involve structured discussion of difficulties encountered in delivering EASE, management of adverse events as well as self-care for the staff. Supervision also forms an integral part of continued training (eg, through role-plays and associated teaching methods).

#### Competency and fidelity

Before and after the training of potential EASE providers, competency of the delivery agents will be evaluated using an adapted version of the Enhancing Assessment of Common Therapeutic factors (ENACT) rating scale.^18^ The ENACT scale is an 18-item assessment for common factors in psychological treatments, including task-sharing initiatives with non-specialists across cultural settings. School counsellors will also record checklists for each session as a measure of self-rated fidelity. An EASE specific checklist and four items assessing facilitation skills will be used to assess treatment fidelity and competency in a random sample of 10%–15% of directly observed sessions for each school counsellor.

#### Wait-list control

The wait-list control participants will receive usual care for the duration of their enrolment in the study. They will receive EASE immediately after trial evaluation on the basis that the results of the study demonstrate positive findings.

#### Outcome measures

Outcome measures will be administered with the adolescents and their parents at baseline, 1-week and at 3 months’ postintervention delivery. Assessments will be conducted by the trained AT who will be blind to allocation status of the participants. See outcomes measures table 1 given below for the details. All outcome measures have been translated in Urdu and adapted to suit the local cultural context as part of the associated feasibility study (trial registration NCT04254393).^12^

**Table 1 T1:** Schedule of assessments

Sr. no	Outcomes	Time points			
		Screening	Baseline	Immediate (1-week) postintervention follow-up	3 months postintervention follow-up
Primary outcome (child’s level)					
1.	PSC	X	X	X	X
Secondary outcomes					
At child’s level					
2.	RCADS		X	X	X
3.	Somatic symptoms		X	X	X
4.	SPSI-R		X	X	X
5.	PESS		X	X	X
6.	PHQ-9		X	X	X
7.	SWEMWBS		X	X	X
8.	PedsQL		X	X	X
9.	PaedS				X
10.	PSYCHLOPS-Kid		X	X	X
At caregiver’s level					
11.	PedsQL-family impact		X	X	X
12.	CSRI		X		X
At both child and caregivers’ levels					
13.	APS		X	X	X
14.	SUQ		X	X	X

APS, Alabama Parenting Scale; CSRI, Client Services Receipt Inventory; PaedS, Paediatric Self-Stigmatisation Scale; PedsQL, Parent-rated Paediatric Quality of Life; PESS, Perceived Emotional/Personal Support Scale; PHQ-9, Patient Health Questionnaire; PSC, Paediatric Symptoms Checklist; PSYCHLOPS-Kid, Perceived Psychosocial Profile; RCADS, Revised Children’s Anxiety and Depression Scale; SPSI-R, Social Problem-Solving Inventory-Revised Short Form; SUQ, Strategy Use Questionnaire; SWEMWBS, Short Warwick Edinburgh Mental Well-being Scale.

### Primary outcome

#### Psychosocial distress

The primary outcome in this study is change in the scores of adolescent psychosocial distress at 3-month postintervention. Adolescents’ psychosocial distress will be measured at baseline, immediate (1 week), and at 3 months postintervention delivery in both arms using the PSC.^19^ The youth version of PSC has 35 items and three subscales; Externalising, internalising and attention problems with cut-offs of 7, 5 and 7 respectively. Items are rated on a three-point Likert scale (0=never, 1=sometimes, 2=often). Total score is calculated by summing the responses of all items. The recommended cut-off for administering PSC for adolescents in a new setting is ≥28.^20^ The cut-off score of ≥28 has been validated in the same study setting previously.^9^

### Secondary outcomes

The Revised Children’s Anxiety and Depression Scale (RCADS). The RCADS-25^21^ is a 25-item scale that measures levels of anxiety and low mood. The scale has two subscales (total anxiety and total depression) and an overall score. All items assess the frequency of symptoms and are rated on a four-point Likert scale. Each item is scored as 0 (never), 1 (sometimes), 2 (often), or 3 (always). Response values for each subscale is summed for calculating raw summary score.Somatic symptoms checklist. The somatic symptoms checklist will be used to measure stress management among adolescents. It consists of 10 items, rated on a three-point scale (0=not true, 1=somewhat true, 2=very true or often true) based on the occurrence of the symptoms. Total score is calculated by summing the responses of all items. Higher score indicates frequent occurrence of somatic symptoms.The Social Problem-Solving Inventory-Revised Short Form^22^ is a self-reporting questionnaire with 25 items. It consists of five subscales with five items each. Two of these subscales, ‘positive problem orientation’ and ‘negative problem orientation’, assess functional and dysfunctional cognitive and emotional orientations towards solving problems. The three remaining subscales, ‘rational problem-solving’, ‘impulsivity-carelessness style’ and ‘avoidance style’, assess problem-solving skills and behavioural style. The total score of this scale varies between 0 and 20 points. Highest scores correspond to better social problem-solving abilities. Social Problem-Solving Inventory-Scale has been used with adolescents in various countries including India and Pakistan.^23^The Perceived Emotional/Personal Support Scale^24^ assesses perceived emotional support. Respondents are instructed to list the gender and first initial of three important people in each of three relationship categories: family members, non-family adults and friends. Using a four-point scale (hardly at all to very much), respondents answer the following questions about each person listed: ‘How much do you talk to them about personal concerns?’ ‘How close do you feel to them?’ and ‘How satisfied are you with the help and support they give you?’ How much do they talk to you about their concerns? Three support variables are created by averaging all ratings for all persons listed within each relationship category: perceived support from family, non-family adults and peers. Scores range from 1 to 4.Patient Health Questionnaire (PHQ-9). PHQ-9, adapted for adolescents^25^ will be used to assess depressive symptoms and severity among adolescents. Items are rated on a four-point Likert scale with 0=not at all, 1=several day, 2=more than half the days, 3=nearly every day. Total score is calculated by summing the responses of all items. Higher score indicates higher incidence of depressive symptoms. PHQ-9 total score for the nine items ranges from 0 to 27.Short Warwick Edinburgh Mental Wellbeing Scale (SWEMWBS). SWEMWBS^26^ is a brief questionnaire designed to measure mental well-being of children and adolescents over the past 2 weeks. It consists of 7 items rated on ‘none of the time’ to ‘all of the time’. The SWEMWBS is scored by first summing the score for each of the seven items and then transforming the total raw scores to metric scores using the SWEMWBS conversion table. The scores range from 7 to 35 and higher scores indicate higher positive mental well-being.^27^Parent-rated Paediatric Quality of Life (PedsQL). Parent-rated PedsQL^28^ will be used to measure child’s health related quality of life during the past month. The scale measures child’s quality of health on four subscales namely, physical functioning, emotional functioning, social functioning and school functioning. The items are rated on four points Likert scale ranging from^1^ ‘no problem’ to^4^ ‘almost always a problem’. Items are then reverse-scored and linearly transformed to a 0–100, so that higher scores indicate better quality of life. This tool yields a total score (of all 23 items) and domain scores including physical health summary score (eight items), psychosocial health summary score (10 items) and school functioning score (five items).Paediatric Self-Stigmatisation Scale (PaedS). The PaedS, is a scale developed for measuring stigma in children and adolescents.^29^ It consists of four subscales that measure societal devaluation, personal rejection, self-stigma and secrecy of receiving mental health treatment. The personal rejection subscale (five items) of the PaedS will be used in this study. The items are rated on four-point Likert scale, where higher scores indicate greater stigmatisation. The tool has been validated for the content and previously used in Pakistan.^30^Peds-QL-Family impact module. Peds-QL family impact module^31^ will be used to assess parents’ health related quality of life. PedsQL family impact module is a 36-item scale that measures quality of life on six subscales namely; physical functioning, emotional functioning, social functioning, cognitive functioning, communication, worry, daily activities and family relationships. Items are rated on a five-point Likert scale (0=never to 4=almost always). Total score is calculated by summing all 36 items divided by the number of items answered. Higher scores indicate better functioning (less negative impact).^28^Alabama Parenting Scale. Alabama parenting scale^32^ will be used to measure parenting practices. Alabama parenting scale is a 42-item measure that encompasses five dimensions of parenting that are relevant to the aetiology and treatment of children’s’ and adolescents’ problems^1^: positive involvement with children,^2^ supervision and monitoring,^3^ use of positive discipline techniques,^4^ consistency in the use of such discipline and^5^ use of corporal punishment. Items are rated on a five-point Likert scale (1=never to 5=almost always). Total score is calculated by summing all items.^33^Strategy Use Questionnaire (SUQ). SUQ^34^ is designed to measure the use of coping strategies (identifying emotions and using relaxation technique, behavioural activation, problem-solving at child and understanding child’s internalising problems, using active listening skill, spending quality time with children, punishing child or using unhealthy disciplinary strategies and using relaxation technique at caregivers). Each item is scored on a frequency scale ranging from 0 (never) to 4 (all of the time). Total score is calculated by summing all items.Health Services Utilisation. The cost of health services utilisation from the time proceeding assessment will be assessed with the adapted Client Services Receipt Inventory (CSRI).^35^ It has been adapted to use for the families of children with psychosocial distress. It measures the utilisation of various health and social care services including time and opportunity losses by the families in the care of their child with psychosocial distress.

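### The PedsQL Family Impact scoring rule, as written, does not agree with its stated direction (higher = better) if the items count problems

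*Protocol article*

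**What the plan says.** All of the relevant text is in the protocol article under Secondary outcomes. The module's purpose is given as: "Peds-QL family impact module^31^ will be used to assess parents’ health related quality of life". Three further statements follow.

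- Item coding: "Items are rated on a five-point Likert scale (0=never to 4=almost always").
- Total score, then direction: "Total score is calculated by summing all 36 items divided by the number of items answered. Higher scores indicate better functioning (less negative impact").

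The entry does not mention reversing items or rescaling them.

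The parent-rated PedsQL, described in the same section, is handled differently. There, "Items are then reverse-scored and linearly transformed" to a 0–100 range, and the article presents higher-is-better as the result of that step.

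The Family Impact entry also says that the module "measures quality of life on six subscales namely; physical functioning, emotional functioning, social functioning, cognitive functioning, communication, worry, daily activities and family relationships". It announces six subscales and names eight.

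Caregivers' well-being is part of the aim at the end of the Introduction and of the secondary hypotheses. In Table 1 the only measures listed solely at caregiver level are this module and the service-use inventory.

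**The concern.** The three statements give a complete scoring rule and then a reading of the result. If an item asks how often a difficulty occurs, a higher code means more difficulty and a higher mean means more burden. The stated reading says the reverse.

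The score appears to be the trial's quantitative measure of caregiver well-being. If a programmer follows the printed formula and an author follows the printed direction, a benefit to caregivers would be reported as harm, and harm as benefit. The validation described under Randomisation and blinding would probably not catch this: it uses dummy randomisation codes, which carry no true treatment effect, so an effect in the wrong direction would not stand out.

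**Working it through.** The article gives no numerical result to reproduce, so the check is whether the written rule produces the stated direction.

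**Inputs.** From Secondary outcomes: 36 items, each coded x = 0 to 4, and a total equal to the sum divided by the number answered. Assumption: the items are problem-worded, because the article does not give their text. This is varied in step 4.

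**1. Formulas**, with n the number of items answered:
- as written: W = Σx / n
- reversed: R = Σ(4 − x) / n = 4 − W
- reversed and rescaled to 0–100: R100 = 25 × R = 100 × (4 − W) / 4

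**2. Results if every item is problem-worded**

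| Responses | W (as written) | R (reversed) | R100 |
|---|---|---|---|
| All never (no burden) | 0.0 | 4.0 | 100 |
| All almost always (maximum burden) | 4.0 | 0.0 | 0 |
| 18 items at 3, 18 at 2 | 2.5 | 1.5 | 37.5 |
| 18 items at 2, 18 at 1 | 1.5 | 2.5 | 62.5 |

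Under the written rule, the caregiver with no burden gets the lowest score. An improvement from the third row to the fourth lowers W by 1.0 and raises R by 1.0.

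A smaller illustrative change, with values chosen only to show the rule: W falling from 2.0 to 1.6 gives R100 = 100 × (4 − 2.0)/4 = 50, then 100 × (4 − 1.6)/4 = 60. That is a gain of 10 points on the reversed scale, but it would be read as a decline under the printed direction.

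**3. Effect on the treatment contrast.** Since R = 4 − W for each caregiver, even with unanswered items, replacing W by R (at baseline and follow-up alike) in the planned linear mixed model changes only the sign of the treatment coefficient. Its absolute value, standard error and p-value stay the same. Rescaling to 0–100 multiplies the coefficient and its standard error by 25 and leaves the p-value unchanged.

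**4. Dependence on item wording.** Let k of the 36 items be positively worded. A fully burdened caregiver then scores W = 4(36 − k)/36, and an unburdened one scores W = 4k/36.

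| k | W, fully burdened | W, unburdened | Direction of written score |
|---|---|---|---|
| 0 | 4.0 | 0.0 | higher = worse |
| 9 | 3.0 | 1.0 | higher = worse |
| 18 | 2.0 | 2.0 | none |
| 27 | 1.0 | 3.0 | higher = better |
| 36 | 0.0 | 4.0 | higher = better |

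The written rule gives the stated direction only if more than half of the items are positively worded. Nothing in the article supports that. The module's name, its worry domain and the gloss about negative impact point to problem wording.

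**The case against.** The strongest reply is that the article leaves reversal out without ruling it out. Nowhere does it say that raw items will be analysed. The direction sentence cites the same reference as the parent-rated PedsQL, for which reversal is stated, so the Family Impact entry may be a shortened account of the same scoring. The article defers analysis detail to a statistical analysis plan that is to be finalised before unblinding, and item-level scoring is often left to such a plan or to a scoring manual. The item text is not given either, and several domain names, such as communication and family relationships, are neutral.

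Most of this stands, and it limits the point. A reader might infer that the caregiver result will be reported backwards. The document does not support that: it would require that reversal is in fact omitted and that the printed direction is then applied to the raw mean. It is equally possible that reversal will be done and only the description is incomplete.

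The reply does not remove the inconsistency. The article goes beyond leaving scoring to another document: it prints a formula for the total, and on the natural reading of the items that formula does not yield the direction printed beside it. The contrast with the parent-rated PedsQL shows that the authors state reversal where they consider it needed.

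**Conclusion.** The point holds as an inconsistency between a stated scoring rule and its stated interpretation. It rests on one assumption, that most of the items count problems, which the article suggests but does not confirm.

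If the rule is applied literally and the result is read literally, the sign of the effect on this outcome is reversed. With all items worded the same way, its size and p-value are unaffected. The consequence is confined to one of the 13 secondary measures in Table 1. The primary PSC outcome, the power and the error rates are untouched. It still deserves correction, because caregiver well-being is a named aim and this module appears to be its main measure.

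The count of six subscales followed by eight names is clerical. The entry defines only a total score for the module, so the miscount has no stated analytic effect and adds no weight to the scoring point.

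**What to change.** Either of two one-line changes resolves the conflict:

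- state that problem-worded items are reverse-scored before averaging over the items answered, so that higher is better; or
- keep the raw mean and state that higher scores mean more negative impact.

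A 0–100 transformation is optional. It would match the parent-rated PedsQL but is not needed to settle the direction.

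Whichever is chosen, confirm the item wording against the questionnaire in use and check that the analysis program and results tables follow the same direction. A simple test is to run two artificial records, all never and all almost always, through the scoring code. Correct the subscale count to match the eight domains listed. The cost is a line of text and a program check, with no new data.

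### The parenting-scale total and the caregiver Strategy Use Questionnaire total add harmful to helpful behaviours with no reversal and no stated direction, so neither total can be read as better or worse and a benefit is diluted

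*Protocol article*

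**What the plan says.** All the scoring text is in the protocol article, under Secondary outcomes.

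- **APS.** "Alabama parenting scale is a 42-item measure that encompasses five dimensions of parenting". The first dimension named is "positive involvement with children". Supervision and monitoring, positive discipline and consistency of discipline follow, and the list closes with "use of corporal punishment. Items are rated on a five-point Likert scale (1=never to 5=almost always). Total score is calculated by summing all items".
- **SUQ, child content.** "identifying emotions and using relaxation technique, behavioural activation, problem-solving at child".
- **SUQ, caregiver content.** Understanding the child's internalising problems, active listening and quality time are listed, and then "punishing child or using unhealthy disciplinary strategies and using relaxation technique at caregivers".
- **SUQ scoring, both versions.** Each item is "scored on a frequency scale ranging from 0 (never) to 4 (all of the time). Total score is calculated by summing all items".

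Neither description contains a reversal step or says which end of the total is favourable. For the parent-rated PedsQL the same section does give a reversal step ("Items are then reverse-scored and linearly transformed to a" 0–100 scale) and a direction.

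Table 1 schedules both the APS and the SUQ for child and caregiver, at baseline and at both follow-ups.

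**The concern.** On a frequency scale, a harmful behaviour and a helpful one move in opposite directions when parenting improves. A plain sum treats them alike. Two consequences follow:

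1. **Direction.** A higher total may mean more positive discipline, more corporal punishment, or both. Without item-level results, a between-arm difference cannot be called benefit or harm.
2. **Sensitivity.** Any fall in harmful behaviour is subtracted from the gain in helpful behaviour.

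The scales bear on what the trial sets out to show. The caregiver–adolescent relationship appears in the study aim and the secondary hypotheses, the caregiver sessions teach active listening, quality time and praise, and the APS is the only instrument described as measuring parenting practices. If the rule stays open until data are seen, the choice of scoring could also follow the results.

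**Working it through.** The article gives no range, SD or expected effect for either total, so there is no stated figure to reproduce. The check is score arithmetic.

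**Inputs from the article**
- APS: k = 42 items scored 1 to 5, in five dimensions. As labelled, four are helpful and one (corporal punishment) is harmful.
- Caregiver SUQ: five content areas scored 0 to 4. As listed, four are helpful and one is harmful.
- Child SUQ: no harmful content is listed.

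**Assumptions, because the article does not give them:** the number of harmful items h, the size of the shift per item, and the inter-item correlation r.

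**Step 1: direction (no assumptions).** Under the stated rule the APS total runs from 42 × 1 = 42 to 42 × 5 = 210.
- One positive-discipline item rises by 1 and one corporal-punishment item falls by 1: the plain sum changes by +1 − 1 = 0, and the reverse-scored sum by +1 + 1 = +2.
- One corporal-punishment item rises by 1 and nothing else changes: the plain sum changes by +1, the same as for one more point of positive discipline.

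**Step 2: raw dilution, equal shifts.** Let every item move by d in the beneficial direction.
- Plain sum: (k − h)d − hd = (k − 2h)d
- Reverse-scored sum: kd
- Share kept: 1 − 2h/k

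| Case | Share kept |
|---|---|
| One of five equally weighted areas harmful | 1 − 2/5 = 60% |
| APS, h = 3 | 1 − 6/42 = 86% |
| APS, h = 8 | 1 − 16/42 = 62% |
| APS, h = 14 | 1 − 28/42 = 33% |
| APS, h = 16 | 1 − 32/42 = 24% |
| APS, h = 21 | 1 − 42/42 = 0% |
| Child SUQ as listed, h = 0 | 100% |

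**Step 3: standardised dilution.** With unit-variance items and equal correlation r in benefit-oriented coding, the effect size of the plain sum relative to the reverse-scored sum is

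(1 − 2h/k) × √{[k(1 − r) + rk²] / [k(1 − r) + r(k − 2h)²]}.

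For example, with k = 42, h = 8 and r = 0.1: 0.619 × √(214.2 / 105.4) = 0.88.

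| Case | r = 0 | r = 0.1 | r = 0.3 |
|---|---|---|---|
| APS, h = 8 | 62% | 88% | 96% |
| APS, h = 16 | 24% | 50% | 73% |
| Five areas, one harmful | 60% | 68% | 80% |

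Correlated items soften the loss, because the plain sum also has a smaller variance.

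**Step 4: unequal shifts.** If harmful content moves by q times the shift of helpful content, five equal areas with one harmful keep (4 − q)/(4 + q) of the raw benefit. That is 100% at q = 0, 3.5/4.5 = 78% at q = 0.5, and 60% at q = 1.

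**The case against.** The strongest reply is that the article is silent on reversal and does not rule it out. The APS scoring sentence carries a citation that is not shown, and the article defers analysis detail to a statistical analysis plan that is also not shown. Stating reversal for the PedsQL proves little, because the section leaves it out elsewhere. The PedsQL family impact module is rated from never to almost always and averaged, yet higher means better. The problem-solving inventory includes dysfunctional subscales, yet its highest scores mean better ability. Both need reversal and neither description says so.

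This stands in part. It means one cannot conclude that the trial will in fact score these scales unreversed. But those two scales state a direction, from which a reader can infer the reversal. The APS and SUQ state none. The article also commits itself to a rule, and that rule needs correcting even if a better one exists in the cited source.

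A reader might go further and infer three things that the article does not support:

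- **That the benefit cancels out or changes sign.** Under equal shifts, cancellation needs half the items to be harmful and a sign change needs more than half. As labelled, one area in five is harmful, and no item counts are given.
- **That harmful and helpful items move equally.** No listed caregiver component names corporal punishment, so the offset may be smaller than in the equal-shift case.
- **That the whole SUQ is affected.** The listed child content is all helpful.

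The article also does not assign the relationship hypothesis to the APS total, so the scoring rule cannot be said to defeat that hypothesis.

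**Conclusion.** The concern holds for the APS total and for the caregiver SUQ total. As written, each adds harmful to helpful behaviours on one frequency scale, with no reversal and no stated direction. That neither total can be interpreted follows from the wording alone.

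The size of the dilution rests on assumptions. With equal shifts and one of five equally weighted areas harmful, 60% of the raw benefit is kept, or 60% to 80% of the standardised effect for r from 0 to 0.3. The share is lower if more items are harmful, and higher if harmful behaviour moves less.

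Severity is moderate. Two of the 13 secondary outcomes in Table 1 are involved, and the primary PSC analysis is untouched. Confidence is tempered because the cited scoring source and the statistical analysis plan are not shown.

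**What to change.** Before unblinding, replace the plain-sum rule for both scales in the statistical analysis plan, and correct the protocol description to match. Either:

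- **Keep the totals.** List the items for which more frequent means worse (corporal punishment and any other negatively worded APS items; the punishment and unhealthy-discipline content of the caregiver SUQ). Reverse-score them before totalling, and state that a higher total means better parenting or strategy use.
- **Or, for the APS, analyse the five dimensions separately**, each with its direction of benefit. This is easier to interpret but replaces one secondary outcome with five. The caregiver SUQ still needs its reversal rule.

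If the cited scoring source already specifies reversal, it is enough to say so and state the direction. The cost is a few sentences and a few lines of scoring code. No new data are needed, since the totals can be recomputed from the item responses.
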